**Fig. 1 Fig1:**
[figure not shown]
ORRCDS tool flow chart. ^a^ Narcotic score. ^b^ This flow chart only applies to Rx opioid risk. Non-Rx opioid substance screening may be feasible under other circumstances. ^c^ WHO Alcohol, Smoking, and Substance Involvement Screening Test prescription opioid use risk assessment. ^d^ Pain, Enjoyment, General Activity. ^e^ Brief intervention for prescription misuse. ^f^ Brief intervention for treatment linkage. ^g^ Treatment. ^h^ Prescription Drug Monitoring Program

**Table 1 Tab1:** GUIDE framework areas of outcome assessment

Domain	Outcome
Domain 1: Context	Tool can achieve the defined quality objectives
	The quality of the patient data is adequate
	Stakeholders and users accept tool
	Tool can be added to the existing workload, workflows and systems
Domain 2: Content	The content provides trustworthy evidence-based information
	The decision support is relevant and accurate
	The decision support provides an appropriate call to action
	The amount of decision support is manageable for the target user
Domain 3: High quality user access	The system is easy to use
	The decision support is well delivered
	The system delivers the decision support to the right target person
	The decision support is available at the right time
Domain 4: Implementation	Information to users about the tool system and its functions is appropriate
	Other barriers and facilitators to compliance with the decision support advice are assessed/addressed
	Implementation is stepwise and the improvements in the tool are continuous
	Governance of the tool implementation is appropriate

The *organizing content* step of GUIDES involved our study investigators as well as pharmacy chain partners laying out all of the ORRCDS content. Briefly (see greater details in the intervention section below), ORRCDS will categorize patients into low, moderate, and high risk. Moderate- and high-risk status based on risk metric scores will be confirmed by a brief self-report assessment (i.e., the ASSIST prescription opioid risk subscale; [30, 31]. These measures were selected given their clinical utility while at the same time being able to accommodate the pharmacy locations and related demands in terms of brevity. False positive patients will be assessed for pain (i.e., the Pain, Enjoyment of Life and General Activity scale [PEG] [36]) and provided resources. Moderate risk patients will be provided with a brief motivational intervention to reduce opioid risk behaviors and given resources—including naloxone referral. High risk patients will be provided with a warm handoff to their primary care provider delivered in the style of a brief motivational intervention to discuss addiction and other treatment options. These patients will also be provided a naloxone referral for a kit to be mailed to them free of charge (see Fig. 1). The content for each risk level was created by developing scripts utilizing brief motivational intervention principles coupled with normative feedback.

The *ensuring high quality user access* step included adapting the existing PDMP platform in collaboration with PDMP and pharmacy partners to ensure screening, motivational intervention/feedback, naloxone recommendation, and warm handoff/treatment linkage tools are easy to use, well-delivered, and activate at optimal times. This has involved an iterative approach with the investigative team presenting ideas and designs for ORRCDS, incorporating those ideas and designs into mock-up slides, reviewing these slides with investigators and pharmacy/PDMP leaders, and then revising the mock-up slides based on feedback.

The final step is *implementing the tool*, which entails two parts. The first is actual tool implementation within the PDMP and pharmacy chain systems. ORRCDS implementation followed the pharmacy chain standard 3-phase approach: (1) pilot site initiation over 1 month; (2) receive feedback from staff/make needed adjustments; and (3) full study testing thereafter. The second part established a training module with the chain pharmacy required for pharmacy staff before site initiation of the intervention (see details below).

***Measurement and analysis***. Objective 1 will be assessed using the GUIDES evaluation framework. This framework includes 4-items per above specified domains, each with a 7-point Likert scale for scoring [32]. This tool will be administered to study stakeholders including investigators, corporate leaders from pharmacy sites and PDMP partners, and a National Institute on Drug Abuse Scientific Officer (assigned to the project by virtue of the cooperative agreement funding mechanism). We will also utilize the System Usability Scale, a brief 10 item measure of perceived computer-based program usability [37, 38], to assess the yes/no go-live readiness of ORRCDS. This assessment will be administered to pilot pharmacy site staff who utilize the tool.

Frequencies, percentages, and measures of central tendency will be employed to assess results from the GUIDES responses. Specifically, each of the above Likert scale items will be described using mean and standard deviation as well as median and interquartile range. For the supporting items, which are yes/no responses (not shown herein), we will calculate frequencies and percentages to characterize responses to these items. For the System Usability Scale, we will summarize the overall score. A score of 68 or higher is considered the cut off for yes/no usability [39, 40]. Having the subjective GUIDES assessment as well as the objective System Usability Scale provides rich insights for the investigative team into the readiness of ORRCDS and avenues needed for improvement before full trial launch.

### Objective 2: Testing the ORRCDS

***Design***. To accomplish the second objective of this study of assessing the impact of the ORRCDS tool on patient opioid risk, our study team will conduct a type-1 implementation mixed methods study using a 2-arm parallel group clustered randomized design. This design clusters patients within pharmacy sites, randomized on a 1-to-1 basis to the ORRCDS vs. usual care. We chose the cluster design given its advantages over patient-level randomization and the length of time required by stepped-wedge designs. Regarding patient level randomization, given the real world application of this tool, training staff to deliver the intervention to only some patients within sites and not others would create a greater risk for condition contamination compared to randomizing by site. The cluster design will reduce the possibility of patients being exposed to both conditions, thus preventing contamination. Regarding length of time, a stepped-wedge design that would attempt intervention rollout in 80 busy pharmacy sites would require a prohibitive amount of time for site intervention delivery initiation, intervention utilization, and follow up.

The randomization will be stratified by zip code poverty level and total pharmacy volume of medication dispensed. Stratification by dispensing volume will ensure an even distribution of higher vs. lower volume stores in each condition—given that high volume sites may be more likely to not intervene with each patient given more intense workload. Advantages of site- vs. patient-level randomization include strengthened internal validity from mitigation of potential condition contamination as well as lower costs—given the number of sites and patients involved herein. ORRCDS will be evaluated within two divisions of a pharmacy chain (*n* = 40 intervention pharmacies/*n* = 40 usual care pharmacies) in the state of Ohio. This design includes a 6-month enrollment phase and a 6-month follow up observation phase (see Fig. 2).

**Fig. 2 Fig2:**
[figure not shown]
Study design. ^*^ Opioid risk reduction clinical decision support

***Study population***. Data from patients within pharmacy clusters will be utilized for analysis. Those patients prescribed an opioid medication, seeking opioid prescription dispensation in a study pharmacy, ≥ 18 years of age, and who have an opioid risk metric of moderate or higher will be included in the study cohort. Those solely receiving buprenorphine formulations for opioid use disorder treatment, without an additional dispensation of a pain medication during the study intervention exposure period or those that received the majority (more than 50%) of their opioid medication dispensations (other than buprenorphine) from non-study pharmacies will be excluded. These data will be obtained from the PDMP database for the state based on a waiver of consent approval from the University of Utah Institional Review Board.

***Interventions***, ***training***, ***and supervision***. Discussed briefly above, the ORRCDS condition involves ORRCDS alerting the pharmacist during the drug utilization review process that a potentially at-risk patient has an opioid medication in queue for pickup; these alerts are based on the previously identified thresholds from the PharmScreen preliminary study [10]. Patients identified as moderate or high risk would receive confirmatory opioid misuse screening. Those identified as low-risk on confirmatory screening will receive auxiliary pain screening on the PEG [36]. Patients reporting moderate/high pain with low opioid risk will receive non-opioid pain management information/education [41]; such education may increase the utilization of non-opioid pain management strategies [42].

Patients with moderate risk on confirmatory opioid misuse screening will receive a brief motivational intervention incorporating normative feedback that targets behaviors associated with opioid misuse (e.g., early refills of opioid medication, seeking multiple opioid prescriptions) coupled with naloxone recommendation and referral. The ORRCDS tool is designed to assist pharmacists in systematically assessing and intervening in cases of risky prescription opioid use and management. This tool will guide the pharmacist through an evaluation of the patient’s risk factors and potential barriers to change, employing motivational interviewing techniques to engage the patient in exploring safety driven behavior change. The risk factors targeted for intervention include, as listed above, opioid dosages, overlapping benzodiazepines and opioid medications, overlapping opioid medications, and numbers of prescribers and pharmacies utilized by patients. Based on the assessed risk level, the tool facilitates a warm handoff to primary care and encourages the patient and primary care provider to discuss a connection to specialized treatment when possibly needed. This approach aims to effectively address opioid misuse while fostering patient-centered care.

In at least four separate clinical trials (*N* = 32, *N* = 62, *N* = 126, *N* = 204 [9, 43–45]) with patients receiving brief motivational interventions to reduce opioid medication misuse/misuse behaviors, study results showed significant improvements [9, 43–45]. In either scenario of moderate or high risk, the pharmacist’s goal is to assist the patients in making health behavior changes to reduce risk—the goal is not to deny or take away access to opioid medication treatment, which could result in detrimental unintended consequences [46–48].

Those with confirmed high risk will receive a warm handoff delivered in the style of a brief motivational intervention to connect patients by phone to their primary care provider to discuss substance use treatment or other treatment needs (such as pain management). These patients likewise will receive a naloxone referral. A rich literature shows warm handoff is an evidence-based method for connecting individuals with substance use needs to treatment [49–53]. Patients with elevated risk will receive up to 2 intervention sessions over the course of up to 2 dispensation encounters with pharmacists—interventions will be similar each session if risk status does not change between encounters. The maximum duration for an opioid prescription in Ohio is 90 days.

ORRCDS training will involve pharmacists at the intervention pharmacy sites being emailed brief reading materials regarding the foundational work of this project. Next, a series of web-based, pre-recorded trainings that instruct pharmacists on using the tool will be made available via an electronic education platform. Pharmacists will be required to view the videos to familiarize themselves with the required steps of the intervention. The prereading and recorded videos each last approximately one hour for a total of two hours. Post tests will be administered in the education platform to ensure material comprehension and retention. Training completion/ attendance will be captured by the training platform.

The study team will also provide monthly supervision sessions during the 6-month intervention period. All intervention site pharmacists will be required to attend at least three of these zoom/telephone sessions to receive booster training from study staff and engage in question-and-answer discussions. Sessions will include didactic material, session examples, and question and answer periods. These supervision sessions will last approximately 30 min and attendance will be captured by study staff leading these sessions.

Intervention delivery performance monitoring will take place weekly by the PDMP vendor providing numbers regarding how many interventions were delivered at unique pharmacies along with the total number of patients in that week who received opioid medications. This will allow the study team to monitor total intervention opportunities and compare those to the actual number delivered and to allow the study investigators to provide site feedback and encouragement in the utilization of the tool.

For the usual care condition, pharmacists are required to perform a universal PDMP review before initial dispensations [54]. Pharmacists are also required to offer brief counseling (e.g., unstandardized information about medication safety) for new/modified prescription therapies [55]. Pharmacists are trained and monitored (via dispensing record system alert) for these requirements by the chain pharmacy partner.

***Outcomes and data collection.*** Study data collection will follow the Reach, Effectiveness, Adoption, Implementation, and Maintenance (RE-AIM) implementation science evaluation framework. Table 2 shows the specific indicators that will be employed in this study, ordered by primary/secondary outcomes [56]. Given the type-1 focus of this study, the primary efficacy outcome will be assessing changes across time for patients’ opioid risk metric level from high to moderate risk or moderate to low risk, see power calculation below. Mentioned above, this metric was validated in CTN-0093, using the WHO ASSIST [10]. Secondary efficacy outcomes will include possible improvements in measures of opioid utilization over time, such as changes in performance on opioid safety measures developed by the Pharmacy Quality Alliance including high opioid dose (greater than or equal to 90 morphine milligram equivalents over 90 days) and overlapping benzodiazepine use (see Table 2 [57–59]).

***Sample size and power.*** We anticipate that ~ 6,600 (based on CTN-0093 pharmacy site estimates) moderate/high-risk patients (evaluated by the opioid risk metric) will be enrolled during the 6-month enrollment phase across the 80 pharmacies. The power calculation is presented for multiple scenarios with different assumptions of intraclass correlation (ICC) and effect size (Table 3). The proposed sample size will provide 96.3% power with 2-sided $$\:{\upalpha\:}$$= 0.05 to detect a 3% or greater difference in responder rate between the intervention arm and control arm. Responders are defined as patients with moderate-risk at baseline who reduce to low-risk or those with high-risk at baseline who reduce to moderate or low-risk at 180 days post last intervention. Risk categories are defined by the thresholds identified in CTN-0093, mentioned above [10]. The power consideration assumes an ICC of 0.05, typical for clustered randomized trials of patient’s outcomes [60, 61]. Importantly, the numbers of pharmacies chosen in this study approximates that of a division within the pharmacy chain. Thus, the results herein will have a real-world reference size within the chain pharmacy corporation.

**Table 2 Tab2:** Reach, effectiveness, adoption, implementation, and maintenance implementation science evaluation framework construct chart

Component	Metric	Data source	Assessment timing	Outcome
Effectiveness	Narcotic Score	PDMP	Preintervention, intervention, postintervention	Primary efficacy
	Fatal overdose	Death certificates	Preintervention, intervention, postintervention	Secondary efficacy
	High dose (PQA)	PDMP	Preintervention, intervention, postintervention	Secondary efficacy
	Multiple providers (PQA)	PDMP	Preintervention, intervention, postintervention	Secondary efficacy
	Overlapping benzo (PQA)	PDMP	Preintervention, intervention, postintervention	Secondary efficacy
	Morphine equivalents	PDMP	Preintervention, intervention, postintervention	Secondary efficacy
	Buprenorphine uptake	PDMP	Preintervention, intervention, postintervention	Exploratory efficacy
	# patients approached	CDS tool	Intervention	Primary implementation
Reach	CDS tool use	CDS tool clicks	Intervention	Primary implementation
Implementation	Perceptions CDS barriers	Pharmacists	Pre/post intervention	Secondary implementation
Adoption	Perceptions CDS barriers Disposition on continued CDS use	Pharmacist partner leader interviews	Pre/post intervention	Secondary implementation
		Pharmacist partner leader interviews	Pre/post intervention	Secondary implementation
Maintenance	Disposition on continued CDS use	PDMP partner leader interviews	Pre/post intervention	Secondary implementation

**Table 3 Tab3:** Power calculation with different assumptions for intra class correlation and effective size

ICC	Design Effect^a^	Total *N*	Effective *N* per arm^b^	Effective Size^c^	Power
0.01	2.24	6600	1471	10%	100
0.01	2.24	6600	1471	8%	100
0.01	2.24	6600	1471	5%	100
0.01	2.24	6600	1471	3%	100
0.01	2.24	6600	1471	1%	97.1
0.03	4.72	6600	698	10%	100
0.03	4.72	6600	698	8%	100
0.03	4.72	6600	698	5%	100
0.03	4.72	6600	698	3%	99.6
0.03	4.72	6600	698	1%	75.5
0.05	7.20	6600	457	10%	100
0.05	7.20	6600	457	8%	100
0.05	7.20	6600	457	5%	100
0.05*	7.20	6600	457	3%	96.3
0.05	7.20	6600	457	1%	57.3
0.1	13.43	6600	246	10%	100
0.1	13.43	6600	246	8%	99.6
0.1	13.43	6600	246	5%	94.7
0.1	13.43	6600	246	3%	78.3
0.1	13.43	6600	246	1%	34.9

^a^Design effect: this is a correction factor that is used to adjust the required sample size due to the clustered randomized design. If a simple randomization is used and the required sample size is N, then to achieve the same power using the clustered randomized design, the sample size should be N times Design effect

^b^Effective *N* per arm: the required sample size to achieve the same statistical power if a simple randomization design is used instead of cluster randomized design. Effective sample size per arm * 2 * design effect = Total N for clustered design

^c^Effective size: the anticipated difference between the 2-intervention arm in responder rate

***Analysis plan***. The primary efficacy endpoint is the responder rate at 180 days post final intervention. We will fit a generalized linear mixed model to relate the primary outcome (i.e., responder status defined based on opioid risk metric) by treatment arm, controlling for baseline covariates including but not limited to the stratification factors, baseline risk level assessment, and other relevant/available patient characteristics, including patient age, sex, insurance status, and location using pharmacy zip code. To model the dichotomous response variable, we will employ the binary distribution with logit link. The random intercept and the unstructured variance covariance matrix will be used to account for within pharmacy correlation. If the model fails to converge, the compound symmetry structured variance covariance matrix will be used.

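### The primary endpoint is timed from the last intervention session, a date that usual-care patients and ORRCDS patients without a session do not have

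*Protocol article*

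**What the plan says.** All references are to the protocol article, Methods, Objective 2, unless stated.

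- **Endpoint.** The Analysis plan states: "The primary efficacy endpoint is the responder rate at 180 days post final intervention". Sample size and power uses the same anchor in the responder definition, which for high-risk patients covers "those with high-risk at baseline who reduce to moderate or low-risk at 180 days post last intervention". The Abstract repeats it. No arm-specific date is given.
- **What an intervention is.** Interventions, training, and supervision: "Patients with elevated risk will receive up to 2 intervention sessions over the course of up to 2 dispensation encounters with pharmacists". The same paragraph adds: "The maximum duration for an opioid prescription in Ohio is 90 days".
- **Usual care.** "For the usual care condition, pharmacists are required to perform a universal PDMP review before initial dispensations". Counselling must also be offered for new or modified therapies. No ORRCDS session takes place.
- **Who is in the cohort.** Study population admits eligible adults "who have an opioid risk metric of moderate or higher will be included in the study cohort". Having been approached is not a condition.
- **Possible non-delivery.** Design explains stratification by dispensing volume on the ground that "high volume sites may be more likely to not intervene with each patient given more intense workload". Table 2 counts the patients approached as an implementation outcome.
- **Calendar.** Design gives six months of enrolment followed by six months of observation. Interventions, training, and supervision refers to a 6-month intervention period.

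**The concern.** A randomised comparison needs the outcome read by a rule that works identically in both arms and does not depend on anything that happens after randomisation. The stated anchor is an event that only the ORRCDS arm can produce, and only in some of its patients. The entry rule and the endpoint therefore do not fit together: patients enter on the metric, but the outcome clock starts at a session.

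The analyst has to fill the gap. One way is to give patients without a session some other date, so that elapsed time from entry to reading can differ by arm. The other is to leave ORRCDS patients without a session out, so that the arm is selected on a post-randomisation event. Elapsed time matters here because the Introduction describes the risk metric as a sum over look-backs of 60, 365 and 730 days. A patient's category is a function of the date on which it is read.

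**Working it through.** **Step 1. Who has the date?** Setting the passages side by side:

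| Group | In the cohort? | Has a session? | Date of last session + 180 days |
|---|---|---|---|
| ORRCDS, one session | yes | yes | defined |
| ORRCDS, two sessions | yes | yes | defined, counted from the second |
| ORRCDS, flagged, never approached | yes | no | undefined |
| ORRCDS, flagged, low risk on confirmatory screening | yes | pain screening, and information where pain is moderate or high, instead of the risk intervention | apparently undefined |
| Usual care | yes | no | undefined |

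The fourth group may not be small. The Introduction reports a Kappa of only 0.35 for the metric against the ASSIST. The article gives no rate for the third or fourth group.

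**Step 2. Days from cohort entry to reading.** Reading day = day of last session + 180.

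- One session at entry: 0 + 180 = 180.
- Two sessions, second at day 90 (assumed gap, equal to the stated maximum prescription duration): 90 + 180 = 270.
- Entry at the start and last session at the end of a 6-month window: about 180 + 180 = 360.
- Usual care, if entry is substituted for the missing date: 0 + 180 = 180.

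So an ORRCDS patient could be read 0 to about 180 days later after entry than a control, and 90 days later in the two-session example. The arm-average lag is the share with a later last session times the gap. The article gives neither. If one third had a second session 90 days on (assumption), it would be 90/3 = 30 days.

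**Step 3. The reading that removes the problem.** If the anchor were the end of the 6-month intervention period, every patient would be read about 360 days after study start. Elapsed time from entry would run from about 180 to 360 days by the same rule in both arms.

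**Step 4. A yardstick, not an estimate.** Sample size and power targets a 3-point difference with 96.3% power. Table 3 gives an effective 457 per arm at an ICC of 0.05. The figure reproduces with the pooled two-proportion formula at a control rate p1 near 0 (the article states none), p2 = 0.03 and mean 0.015:

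- Numerator: 0.03 × √457 − 1.96 × √(2 × 0.015 × 0.985) = 0.6413 − 0.3369 = 0.3044.
- Denominator: √(0.03 × 0.97) = 0.1706.
- Power: Φ(0.3044 / 0.1706) = Φ(1.784) = 0.963.

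Now suppose there is no treatment effect and the reading date alone shifts one arm by b points. The two-sided 5% test rejects with probability Φ(d − 1.96) + Φ(−d − 1.96), where d = b/SE. For b = 0.03 and an assumed control rate of 10%:

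- SE = √((0.10 × 0.90 + 0.13 × 0.87)/457) = 0.0211.
- d = 1.423, and the rejection probability is 29.6%.

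| Shift b (assumed) | Control rate 10% | Control rate 20% |
|---|---|---|
| 1 point | 7.8% | 6.6% |
| 2 points | 16.2% | 11.5% |
| 3 points | 29.6% | 19.7% |

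Nothing in the article says that any of these shifts will occur. The table shows only that a target of 3 points leaves little room for a timing artefact.

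**The case against.** **The text may be condensed.** A journal article leaves detail to the full protocol, and the study-design figure is not available here. A common index date may exist there. This lowers certainty about what will be done, but not about what is written. The article states the anchor three times and applies it to both arms, so this is a stated rule and not a detail left out.

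**A common date is a possible reading.** The 6 + 6-month structure, the pre-, during- and post-intervention timing in Table 2, and the exposure period in the eligibility criteria all allow the end of the intervention period as anchor. A control patient's dispensing encounter could also serve as an equivalent date. This stands as a possibility. The text adopts neither, and its description of sessions per patient points the other way.

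**The cohort definition argues against dropping patients.** A reader might infer that the plan prescribes a treated-only ORRCDS arm. It does not: the cohort and the roughly 6,600 expected patients are counted by the metric, and no per-protocol restriction appears. Selection is a consequence of applying the anchor literally. The Design section says only that non-delivery may be more likely at busy sites.

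**A reader might infer that the bias favours ORRCDS.** The documents do not support this. Old fills leave the look-back windows, but new ones enter, so a patient who keeps filling opioids may stay level or rise. Selecting patients who return and are approached could also work against ORRCDS.

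**A reader might put a size on the bias.** An assumed drift of 0.5 to 2 points per 30 days over a lag of 30 to 90 days would give 0.5 to 6 points. The rate has no basis in the article, 90 days is a maximum prescription length and not an expected gap, and the product gives the lag to every ORRCDS patient when only those with a later last session have it.

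**Conclusion.** The point holds. As written, the primary endpoint has no reading date for the usual-care arm or for ORRCDS patients without a session, although all belong to the cohort. Taken at patient level, the rule leads either to different reading times by arm (day 270 against day 180 in the example) or to selection on session receipt. The example assumes two sessions 90 days apart and controls read at entry + 180 days.

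Because of the metric's look-backs, the reading date can change responder status. The direction and size of any bias cannot be derived from the documents. If the end of the common intervention period was meant, the defect is one of wording and a sentence resolves it. If the full protocol already sets a common date, the published definition should be brought into line with it.

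**What to change.** Define the index date identically in both arms and independently of session receipt, for example the first dispensation at a study pharmacy in the enrolment phase with a moderate or high metric. Read responder status at the same fixed interval from it; index + 180 days fits the 6 + 6-month design. If the end of the intervention period was intended, say so and read everyone at one common date tied to it.

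Analyse every eligible flagged patient by the arm of the index pharmacy, whatever number of sessions was received. Report status at 180 days after the last session only as a descriptive result for the ORRCDS arm.

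The outcome comes from the PDMP database, so the change touches endpoint wording and extraction logic only. The price of index + 180 days is that patients with a second session have less than 180 days of follow-up after it: 180 − 90 = 90 days in the example above. The question becomes risk status 180 days after being flagged, in place of durability after the last session.
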